### Eligibility Criteria

#### Overview

Eligibility criteria were selected to ensure an optimal fit of the study sample with respect to the subsequent implementation of the app in the German health care setting, to meet the requirements of the legal authorities, to minimize the impact of confounding variables, and to ensure comparability with other studies on self-guided digital interventions.

#### Inclusion Criteria

We are including adults with mild or moderate depression according to ICD-10 criteria (F32.0, F32.1, F33.0, and F33.1). Clinical interviews are conducted to confirm the diagnosis. Raters are clinical psychologists and clinical psychologists in training who are not part of the core study team. They administer the short version of the diagnostic interview for mental disorders [52], a short structured clinical interview for diagnosing mental disorders. The interview assesses current and lifetime diagnoses according to the Diagnostic and Statistical Manual of Mental Disorders, Fifth Edition (DSM-5) and ICD-10.

Participants must also be fully legally competent, reside in Germany, and have sufficient German language skills. They must have access to their own smartphone (Android, version 6.0, Google, or iOS, version 13.0 or higher, Apple) and the internet, and be willing and able to use the app regularly and participate in the assessments.

#### Exclusion Criteria

We are excluding individuals who receive outpatient psychotherapy or inpatient treatment for a mental disorder at the point of enrollment or already have such a treatment planned to start within the next 8 weeks. We are also excluding individuals who report changes in antidepressant medication in the past 4 weeks, who report suicidal ideations, or who have a history of bipolar disorder, psychotic disorder, substance use disorder, or suspected substance use disorder. Individuals who report having used the MindDoc App or a comparable digital intervention in the past 12 months will also be excluded.

### Recruitment

Participants are recruited via press releases, social media advertising, and cooperating primary care practices. Recruitment will take place over a period of at least 6 months. It is expected that about 2500 prospective participants will have to be screened, of whom 800 will be invited for a diagnostic interview to determine eligibility.

### Intervention

MindDoc with Prescription is a digital intervention aimed at supporting individuals with mild to moderate mental disorders from the internalizing spectrum, including depression. The app can be used as a low-threshold psychosocial intervention.

MindDoc with Prescription is a risk class I medical device according to Annex VIII, Rule 11 of the Medical Device Regulation (REGULATION (EU) 2017/745 on medical devices). Intended users include individuals with mild and moderate mental disorders.

The app consists of four key components: (1) continuous self-monitoring of symptoms and personal resources (journal), (2) personalized feedback on symptoms and coping strategies (insights), (3) regular overall assessments of emotional health (result), and (4) courses and exercises for psychoeducation and self-management (discover). All content was developed by licensed clinical psychologists based on established guidelines for the treatment of mental disorders.

The journal component allows users to log symptoms and personal information up to 3 times a day, with mood assessments and free text inputs. The insights section provides personalized feedback based on the information recorded in the journal. The result section provides an overall assessment of emotional health every 14 days, while the discover section offers courses and exercises on coping with symptoms, drawing on cognitive behavioral therapy, and other evidence-based treatments. Recommendations for relevant courses are provided based on users’ journal entries. The app is designed to help patients understand and manage their symptoms, promoting self-sufficiency, and empowering them to take control of their mental health.

Participants can contact the study team and the MindDoc customer support by email at any time with questions about app use. Requests will typically be answered within 1 working day.

A detailed description of MindDoc with Prescription is provided in Multimedia Appendix 1. Instructions for use can be viewed on the app manufacturer’s website [53].

### Measures

#### Screening and Diagnostic Interview

The screening questionnaire is designed to assess the inclusion and exclusion criteria described above and includes the depression module of the Patient Health Questionnaire-9 (PHQ-9) [54,55] to assess depression symptom severity, the Alcohol Use Disorders Identification Test (AUDIT) [56] to assess problematic alcohol use, and the Drug Use Disorders Identification Test (DUDIT) [57] to assess drug use. It also contains questions on current and previous treatments and diagnoses, as well as questions on sociodemographic data.

The diagnostic interview is a shortened version of the short version of the diagnostic interview for mental disorders (Mini-DIPS) [52], a short structured clinical interview for diagnosing mental disorders. The interview assesses current and lifetime diagnoses according to DSM-5 and ICD-10 and is used to confirm that participants fulfill the diagnostic criteria for depression and to assess comorbidity.

#### Study End Points

##### Depression Symptom Severity

Depression symptom severity is assessed using the depression module of the PHQ-9 [53,58], a 9-item questionnaire that is part of the Primary Care Evaluation of Mental Disorders (PRIME-MD) diagnostic instrument for common mental disorders [54] and can be self-administered. The questionnaire evaluates each of the 9 DSM-5 diagnostic criteria for depression [59], with scores ranging from 0 (not at all) to 3 (nearly every day). The PHQ-9 is a reliable and valid tool for measuring depression, with a Cronbach α coefficient of .89.

##### Quality of Life

Quality of life is assessed with the Assessment of Quality of Life-8 Dimensions (AQoL-8D) [60]. The 35-item self-rating scale can be used to evaluate the impact of health care services on an individual’s psychosocial quality of life. It measures 6 psychosocial functioning domains and physical autonomy, and has shown high reliability (with a Cronbach α score of .96) and convergent and predictive validity.

##### Anxiety Symptom Severity

Anxiety symptom severity is assessed with the Generalized Anxiety Disorder-7 (GAD-7) [58,61], which is a 7-item tool for detecting symptoms of generalized anxiety disorder as defined in the DSM-5. Each item is rated on a scale from 0 (not at all) to 3 (nearly every day), making it an effective and reliable way to screen for anxiety disorders and assess their severity in both clinical settings and research.

##### Patient Empowerment and Self-Management Behaviors

Patient empowerment and self-management behaviors are assessed with a questionnaire we have developed for our previous study [49,50]. It consists of 10 statement items assessing patient empowerment on a 6-point Likert scale (strongly agree, mostly agree, somewhat agree, somewhat disagree, mostly disagree, and strongly disagree) and 18 question items assessing the frequency of self-management behaviors in the past 8 weeks on a 6-point Likert scale (never, once in a while, less than half the time, more than half the time, most of the time, and all the time). The questionnaire has good internal consistency in data from a previously conducted study. The parallel analysis yields 2 components, and an exploratory factor analysis with 2 factors yields medium to high factor loadings of the respective items on their scales as well as low cross-loadings. Reliabilities (McDonalds ω) are in the good to very good range for both subscales as well as the total scale (ω (self-management)=0.87; ω (empowerment)=0.82; ω (total scale)=0.89). Furthermore, the overall scale of the instrument showed convergent validity in the form of significant correlations (*P*<.01) with further surveyed constructs from health literacy (knowledge of self-help measures: *r*=0.44, 95% CI 0.39-0.49; “first aid skills”: *r*=0.38, 95% CI 0.33-0.43), with attitudes toward mental illness (positive attitudes toward help-seeking behavior: *r*=0.46, 95% CI 0.41-0.51; stigma toward mental illness: *r*=0.30, 95% CI 0.25-0.36), and with the “coping” (*r*=0.40, 95% CI 0.35-0.45) and “relationships” (*r*=0.37, 95% CI 0.31-0.42) subscales of the AQol-8D.

##### Other Measures

Depression symptom severity will also be rated by a clinician (clinical psychologist or clinical psychologist in training), using a short version of the Hamilton Rating Scale for Depression (HAM-D) with 6 items. The chosen version best differentiates between groups with and without treatment compared with other versions [62]. HAM-D is the most widely used clinician-administered depression assessment scale. The rating scale was supplemented with the Structured Interview Guide for the HAM-D (SIGH-D) [63,64]).

The therapeutic alliance is measured with a shortened version of the Working Alliance Inventory (WAI-SR) [65] is used, which contains the 8 items of the dimensions (process and goals).

Negative intervention effects were assessed with the Inventory for Balanced Assessment of Negative Effects of Online Interventions (INEP-ON) [66], which captures negative intervention effects from the patient’s perspective. The questionnaire also assesses whether patients attribute these effects to the intervention or to other factors.

##### Confounding Variables

To estimate the influence of potential confounding variables, additional information is collected (see Textbox 1).

Confounding variables to be investigated in secondary analyses.
**Moderators (to be recorded before randomization)**
Duration of illnessGender and agePsychiatric comorbidityType of depression (first-time, recurrent)Severity of depression (Patient Health Questionnaire-9 sum score at randomization)Prior treatment (antidepressant medication, outpatient psychotherapy, inpatient treatment or day treatment for a mental disorder, and comparable digital interventions for depression based on cognitive behavioral therapy)Personality functioningHealth literacy
**Mediators (to be recorded after 8 weeks and after 6 months, respectively)**
Outpatient visits with psychotherapists or psychiatristsOutpatient visits with general practitionersOutpatient visits with physicians of other specialtiesInpatient treatment for mental disordersChanges in medication use between baseline and follow-upUse of other digital interventions addressing mental health between baseline and follow-upUse of alternative treatment methods (eg, acupuncture, osteopathy, homeopathy, and Reiki) between baseline and follow-upUse of low-threshold psychosocial services (eg, self-help groups, counseling centers, and social psychiatric service) or preventive services (eg, relaxation training) between baseline and follow-upCritical life events between baseline and follow-up

Personality functioning is assessed with the Level of Personality Functioning Scale-Brief Form (LPFS-BF) [67], a brief self-report measure that captures personality functioning in the domains of self and interpersonal pathology and is compatible with the assessment of severity of personality dysfunction according to ICD-11. The German version has high reliability and satisfactory validity. The severity of personality dysfunction was an important predictor of trial discontinuation in a previous study [50].

Health literacy was assessed with the Mental Health Literacy Questionnaire (MHLq) [68], a 29-item scale with 4 dimensions (knowledge about mental health problems, false beliefs or stereotypes, help-seeking and first aid skills, and self-help strategies). Results showed significant differences between individuals with more or less experience with mental health and good internal consistency for the overall outcome.

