### Sample Size

The primary end point is the between-group difference in depressive symptoms (PHQ-9 total score) after 8 weeks. The effect regarding the primary end point will be determined by a 2-tailed *t* test. Based on the results of our previous study, an effect of *d*=0.4 (Cohen *d*) is expected and a dropout rate of up to 60% is assumed. A sample size of 570 participants is required to detect the expected difference at 85% probability and α=5% significance in both intention-to-treat and per-protocol analyses.

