### Statistical Analysis

Data will be described using descriptive statistics (eg, frequencies, mean, median, SD, and IQR) and visualizations (eg, histograms, box plots, and bar charts). Assumptions for statistical tests will be checked (eg, normality by histograms and tests, sphericity by Mauchly test, and equal variance-covariance matrices by Box and Levene tests). App usage will be described according to previously proposed standards for reporting adherence to digital interventions [69], and include days of use and engagement with different features of the app.

Significant baseline group differences will be detected using *χ*^2^ and *t* tests on baseline variables and accounted for in all analyses.

The intervention’s effectiveness will be analyzed using an intention-to-treat approach with multiple imputed data. Missing values from the postsurvey and follow-up survey of nonbinary end points will be imputed using all available information collected at baseline by applying an iterative Markov chain Monte Carlo method based on the initial group assignment. For this purpose, imputations will be calculated for 100, 150, 200, 300, 400, and 500 iterations. Then, the fraction of missing information (FMI) index will be determined for all multiply imputed data sets. The FMI ranges from 0 to 1 (where 1 means that 100% of the information required for the planned conclusions is missing) and is a reliable indicator of the validity of conclusions based on imputed data sets [70]. For the following analyses, the number of imputations that do not result in further improvement in FMI compared to previous imputations will be chosen. Statistical characteristics will be aggregated across the multiply imputed data sets using Rubin’s rules. The comparison of intervention effects on all outcomes will be done using *t* tests.

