In addition to the primary analysis, further sensitivity analyses will be performed. Analyses of intervention effects on all outcomes will be repeated using analysis of covariance, adjusted for baseline scores. In addition, per-protocol analyses excluding participants who violated the protocol will be conducted. The following protocol violations have been prespecified: (1) failure to download the app and complete the onboarding process in the intervention group, (2) reporting of using a similar digital health intervention during the intervention and follow-up period in the control group, (3) reporting of regular psychotherapy during the 8-week intervention period, and (4) noncompletion of postintervention or follow-up assessment. Subgroup analyses will be done to address potential heterogeneity.

To allow for adjustment of the sample size in this study (for lower dropout), an interim analysis can be performed. This can be done once the primary end point of 182 participants is available. With this sample size, the expected effect can be revealed with a probability of 85% at a significance level of α=10%. The interim analysis will be performed blinded, meaning that the variable “group membership” will be replaced by a dummy variable and the blinded data set will be analyzed by a person who is not part of the core study team and is unaware of the group assignment.

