### Impact and Future Directions

With a focus on both symptom reduction and patient empowerment and self-management behaviors, the study will contribute to expanding the evidence base of transdiagnostic low-threshold digital interventions.

Furthermore, the study aims to provide insights into factors impacting the effectiveness of transdiagnostic digital interventions in mental health care. By examining potential moderators and predictors of outcomes, the study will inform decision-making in stepped care and improve mental health care.

General psychopathology and personality dysfunction have previously been shown to predict treatment response in digital interventions, rendering these factors as potential predictors of outcome in this trial. Further, improvement of mental health–related self-management skills and literacy through app usage may constitute an important mediating factor for change in psychopathology. In addition, the detailed assessment of help-seeking behavior and mental health care use may help to disentangle the direct and indirect effects of transdiagnostic digital interventions on mental health.

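### The per-protocol sensitivity analysis selects on completion but its stated models leave out the LPFS-BF, the protocol's own named predictor of discontinuation; adding it is a nearly free, minor improvement

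*Protocol article*

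**What the plan says.** Protocol article, Sample Size: "The primary end point is the between-group difference in depressive symptoms (PHQ-9 total score) after 8 weeks", and "The effect regarding the primary end point will be determined by a 2-tailed *t* test". The planning assumptions are that "an effect of *d*=0.4 (Cohen *d*) is expected and a dropout rate of up to 60% is assumed". The resulting 570 participants are said to serve both the intention-to-treat and the per-protocol analysis.

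Statistical Analysis: all outcomes are compared by t tests. Among the sensitivity analyses, "Analyses of intervention effects on all outcomes will be repeated using analysis of covariance, adjusted for baseline scores". A per-protocol analysis is also listed there, with four prespecified violations. The first, not downloading and onboarding, can occur only in the intervention arm. The second, using a similar digital intervention, is counted only in controls. The third is regular psychotherapy in the 8-week period. The last is "4) noncompletion of postintervention or follow-up assessment". For the primary analysis, missing outcomes "will be imputed using all available information collected at baseline". Baseline variables that differ significantly between groups are to be accounted for in every analysis.

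Confounding Variables: personality functioning (LPFS-BF) is listed among the moderators recorded before randomization, and the text adds: "The severity of personality dysfunction was an important predictor of trial discontinuation in a previous study [50". Impact and Future Directions: "General psychopathology and personality dysfunction have previously been shown to predict treatment response in digital interventions".

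**The concern.** The per-protocol comparison is made among people selected after randomization. The protocol names one measured variable as a predictor of that selection and of response, uses it in the imputation behind the primary analysis, and omits it from the models stated for the other outcome comparisons. If the LPFS-BF drives dropout more strongly in one arm, or dropout rates differ by arm, the completers are no longer balanced on a prognostic variable the trial already holds.

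The design makes arm-dependent selection plausible. Two exclusions apply to one arm only, and controls receive the app only after their follow-up assessment, whereas the intervention arm has it from the start. A gap between the imputed and per-protocol results could then reflect selection on the LPFS-BF rather than adherence to protocol, and the reader could not separate the two.

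**Working it through.** **The plan's own figure.** A two-sample t test with d = 0.4, two-sided alpha 5% and power 85% needs 113.2, so 114 per arm, or 228 completers (power 85.2%). Then 228 / (1 − 0.60) = 570, as stated. The sample size is sound, and the point below does not change it.

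**Inputs.** From the documents: d = 0.4, dropout up to 60% (Sample Size), and about 20% of primary outcomes missing so far (Results). The documents give no dropout by arm and no size for the association of the LPFS-BF with dropout or outcome. These are therefore assumed:
- dropout odds ratio per SD of LPFS-BF of 1.5 in the intervention arm and 1.0 in controls, with equal dropout rates;
- correlation ρ of LPFS-BF with 8-week PHQ-9 of 0.3 to 0.5;
- correlation of LPFS-BF with baseline PHQ-9 of 0.4, and of baseline with 8-week PHQ-9 of 0.5.

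**Step 1, imbalance among completers.** With logistic dropout on a standard-normal LPFS-BF, the completer means differ between arms by Δ = 0.234 SD at 40% retention (0.155 SD if the odds ratio is 1.3) and by Δ = 0.079 SD at 80% retention.

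**Step 2, bias.** For the t test, bias ≈ ρ × Δ. After ANCOVA on baseline PHQ-9, the remainder is close to (ρ − 0.5 × 0.4) × Δ = (ρ − 0.2) × Δ.

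| Dropout | ρ | t test | ANCOVA on baseline score |
|---|---|---|---|
| 60% | 0.3 | 0.3 × 0.234 = 0.070 | 0.1 × 0.234 = 0.023 |
| 60% | 0.4 | 0.4 × 0.234 = 0.094 | 0.2 × 0.234 = 0.047 |
| 60% | 0.5 | 0.5 × 0.234 = 0.117 | 0.3 × 0.234 = 0.070 |
| 20% | 0.3 | 0.3 × 0.079 = 0.024 | 0.1 × 0.079 = 0.008 |
| 20% | 0.4 | 0.4 × 0.079 = 0.032 | 0.2 × 0.079 = 0.016 |
| 20% | 0.5 | 0.5 × 0.079 = 0.040 | 0.3 × 0.079 = 0.024 |

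Large-sample simulation at 60% dropout agrees: 0.073, 0.090 and 0.120 SD for the t test; 0.024, 0.043 and 0.073 SD for the ANCOVA; about 0 once the LPFS-BF is added. Here the bias favours the app; with the odds ratios swapped between arms it runs against it.

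**Step 3, when the bias vanishes or survives.** A separate simulation used a true effect of −0.4 SD, ρ = 0.4 unless stated, and a baseline regression coefficient of 0.5. Bias in SD is given for the t test, the ANCOVA on baseline score, and the ANCOVA with LPFS-BF added:
- Same odds ratio (2) and same dropout rate in both arms, at 20%, 40% or 60%: about 0 in all three.
- Odds ratio 2 in both arms, dropout 70% versus 50%: −0.054, −0.023, about 0.
- Odds ratio 2 versus 1, dropout 60%: −0.149, −0.061, about 0.
- As the last, but LPFS-BF related to outcome only through baseline PHQ-9 (ρ = 0.2): −0.071, about 0, about 0.
- LPFS-BF modifies the effect by 0.1 SD per SD, with odds ratio 2 and 60% dropout in both arms: about −0.04 in all three.

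**Step 4, the baseline-difference rule.** Applied to the randomized sample, it cannot see an imbalance that dropout creates later. Applied to 114 versus 114 completers at two-sided 5%, a t test flags a 0.155 SD imbalance in 21% of trials and a 0.234 SD imbalance in 42%.

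**The case against.** The strongest reply is that this is an unstated covariate in a sensitivity analysis, and such a list normally belongs in an analysis plan that is not shown. That stands in part: the article never says the LPFS-BF will be left out. But it does fix the per-protocol exclusions, the t test for all outcomes and the ANCOVA covariate, so the models as stated can be judged.

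A reader might go further and infer that the per-protocol analysis is biased and that the bias can be removed. The documents support neither. A predictor of discontinuation does not by itself bias a comparison of randomized arms; selection must differ by arm, or the variable must modify the effect. No arm-specific dropout is reported, and equal selection gives zero bias. With odds ratios of 1.5 versus 1.25 at 60% dropout, the ANCOVA remainder is only 0.01 to 0.03 SD. Removal would also be partial at best. The article lists personality functioning as a moderator, and a main-effect covariate does not remove effect modification or other causes of exclusion.

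Nor can it be said that the trial's robustness checks fail. The Abstract also plans sensitivity analyses with additional imputation strategies, and the primary imputation already draws on all baseline data.

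Finally, 20% missing is far below the planned 60%. That is fair, though it concerns the 8-week outcome only. The per-protocol rules also remove people who miss the 6-month survey or meet another exclusion, so per-protocol losses may be larger; the article gives no figure.

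**Conclusion.** The point holds as a minor one. The per-protocol analysis is exposed to a selection bias, partly avoidable, if selection on the LPFS-BF differs by arm. The design makes that plausible but nothing in the documents shows it.

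Against the planned d = 0.4, the assumed 1.5 versus 1.0 contrast gives, at 60% dropout, 18% to 30% of the effect for the t test (0.07/0.4 to 0.12/0.4) and 5% to 18% after baseline-score ANCOVA (0.02/0.4 to 0.07/0.4). At 20% dropout the shares are 5% to 10% and about 2% to 6% (0.008/0.4 to 0.024/0.4). All of this rests on assumed associations, and the direction depends on which arm loses more people with poor personality functioning. The primary analysis and the sample size are unaffected.

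**What to change.** In Statistical Analysis, state that the per-protocol comparison is an ANCOVA adjusted for the baseline score of the outcome and the LPFS-BF total, both recorded before randomization. This costs one sentence and one degree of freedom, with no new data.

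Alternatively, stop counting a missed assessment as a protocol violation, treat it as missing data, and run the per-protocol comparison in the multiply imputed data sets, which already use all baseline information. This option needs one further rule. The violations for other digital interventions and for psychotherapy depend on participants' reports, so the text should say how someone without that report is classified.

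Either way, the write-up should say that effect modification, unmeasured causes of dropout and the arm-specific exclusions can still bias the per-protocol result.
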